#### Analysis of Secondary Efficacy and Exploratory Endpoints

Secondary efficacy endpoints that FSS, FAS, K-PHQ-9 total score change, each pattern identification probability change, and exploratory endpoints K-NIHSS, mRS, K-mBI, K-MoCA total score change are continuous variables, and the average for each measurement, SD, median, minimum value, maximum value will be presented and the difference between the HH333 group and the control group will be tested using repeated measures ANOVA.

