## Methods

### Study Design

This multicenter, double-blind, randomized controlled trial (RCT) aimed to assess the prevention of recurrent ischemic stroke and the safety of HH333 in patients with ischemic stroke induced by small-vessel disease. It was conducted at 3 university Korean medicine hospitals in South Korea: Kyung Hee University Korean Medicine Hospital, Dongguk University Ilsan Korean Medicine Hospital, Wonkwang University Gwangju Korean Medicine Hospital. Within 90 days of onset at baseline, patients will receive HH333 or a placebo, 2 capsules (800 mg) at a time, once a day for 720 days. The clinical effect of HH333 will be evaluated by ischemic stroke recurrence, which is the primary efficacy endpoint, at baseline and on days 30, 90, 180, 270, 360, 450, 540, 630, 720, and 750 after starting the medication. Total scores on the Fatigue Severity Scale (FSS), Fatigue Assessment Scale (FAS), Korean Patient Health Questionnaire (K-PHQ-9), and the probability of each type of Pattern Identification (fire heat, dampness-phlegm, qi deficiency or yin deficiency) will be evaluated as secondary efficacy endpoints at baseline and 90, 180, 270, 360, 450, 540, 630, and 720 days after starting medication. The total scores on the Korean National Institutes of Health Stroke Scale (K-NIHSS), modified Rankin Scale (mRS), Korean Modified Barthel Index (K-mBI), and Korean Montreal Cognitive Assessment (K-MoCA) will also be measured as exploratory endpoints at the same time as the secondary efficacy endpoints. The safety of HH333 will be assessed based on the presence of adverse events at the same time as the primary efficacy endpoints. The enrollment, interventions, and assessments of the study are summarized in Table 1. A schematic of the study process is shown in Figure 1.

**Table 1 table1:** Schedule of enrollment, interventions, and assessments.

Visit	0	1	2	3	4	5	6	7	8	9	10	11^a^	UV^b^
Day	–14^c^	0	25-35	80-100	165-195	255-285	345-375	435-465	525-555	615-645	705-735	745-755	
Informed consent	✓												
Demographic information^d^	✓												
Medical history^e^	✓												
History of ischemic stroke^f^	✓												
Medications^g^	✓												
Physical examination	✓	✓	✓	✓	✓	✓	✓	✓	✓	✓	✓		If needed
Vital sign	✓	✓	✓	✓	✓	✓	✓	✓	✓	✓	✓		If needed
Physical measurements	✓												
Laboratory tests^h^	✓												
Electrocardiogram	✓		✓	✓	✓	✓	✓	✓	✓	✓	✓		If needed
Evaluating inclusion and exclusion criteria	✓												
Randomized allocation		✓											

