### Exploratory Endpoints: K-NIHSS, mRS, K-mBI, and K-MoCA

The NIHSS is a tool for assessing neurological deficits resulting from stroke developed by the National Institutes of Health [32] and is currently the most widely used tool for stroke severity assessment, with a Korean version validated and used [33]. It comprises 15 questions in 11 checkpoints, each of which is scored on a scale of 0 to 4, with a total score calculated, with higher scores indicating higher severity. The mRS is a tool developed by van Swieten et al to assess the degree of disability in patients with stroke [34] and is currently the most widely used stroke functional assessment scale [35]. It is rated on a scale of 0 to 6, with higher scores indicating more severe impairment. The mBI is a tool to assess independence in activities of daily living after stroke developed by Shah et al [36], and translated with validation in Korean [37]. It contains 10 questions, each rated on a scale of 0 to 5, 0 to 10, or 0 to 15, with a higher total score indicating a lower dependency. The MoCA is a tool that examines cognitive function and was originally developed to identify mild cognitive impairment [38] but is now widely used for cognitive impairment caused by stroke, and the Korean version has been validated and used [39]. It consists of visuospatial and executive (5 points), naming (2 points), attention (6 points), language (3 points), abstraction (2 points), delayed recall (5 points) and orientation (6 points). The perfect score is 30, with a higher total score indicating higher cognitive function. Investigations were conducted during the administration period on days 0 (baseline), 90, 180, 270, 360, 450, 540, 630, and 720.

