### Sample Size

In previous studies, ischemic stroke recurrence rates of 12.5%-12.8% over 24 months with conventional antiplatelet therapy (aspirin or dipyridamole) [22] and 1.7% over the same period with HH333 [19] were reported. Therefore, the sample size was 106 patients per group and 212 patients in total at 2 years with a control group (P_2_=0.125-0.128), HH333 group (P_1_=0.017), a significance level (α) of 5% and a target power of 80%. Finally, a dropout rate of 10% was considered, resulting in a sample size of 118 patients per group for a total of 236 patients.

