### Statistical Analysis

All statistical analyses were two-sided with a 5% significance level. The statistical program SAS (version 9.4 or more, SAS Institute) was used for the analysis. If at any point there are missing values or participants are dropped before the end of the study, the data will be treated as missing data. All data obtained from the participants were analyzed in 3 forms: full analysis set, per-protocol set, and safety set. Efficacy analysis will be conducted using the results of the full analysis set as the main analysis, and a per-protocol set analysis will be conducted separately to evaluate whether there are differences from the full analysis set results. Safety analysis was performed on the safety set and the safety of the study medications was evaluated. The full analysis set includes all data from participants with at least one efficacy assessment at the primary outcome after taking the study medication. The per-protocol set included participants who were eligible for full analysis and successfully completed the study. The safety set included all data from participants who received at least one dose of the study medication.

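### The mRS, a single ordered grade from 0 to 6, is analysed as a continuous change score, without day-0 mRS as a predictor and without counts per grade: valid, but cheaply improved

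*Protocol article*

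**What the plan says.** The Exploratory Endpoints section of the protocol article describes the K-NIHSS, K-mBI and K-MoCA as totals built from several questions or domains. The mRS has no component items: "It is rated on a scale of 0 to 6, with higher scores indicating more severe impairment".

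The Analysis of Secondary Efficacy and Exploratory Endpoints section puts all four scales into one list: "exploratory endpoints K-NIHSS, mRS, K-mBI, K-MoCA total score change are continuous variables". The planned summaries at each visit are the mean and SD together with the median and range. On the comparison of the arms, the section says that "the difference between the HH333 group and the control group will be tested using repeated measures ANOVA".

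The mRS is recorded at day 0 and at days 90, 180, 270, 360, 450, 540, 630 and 720, which gives eight post-baseline visits. Its rank is clear: the four scales "will also be measured as exploratory endpoints at the same time as the secondary efficacy endpoints".

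The Demographic Information Analysis section makes a baseline variable a covariate in the efficacy analysis only if the two arms differ significantly on it. Frequencies and percentages are promised there for categorical baseline data. Neither a per-grade table nor an ordinal analysis is given for the mRS.

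**The concern.** Three features of the plan meet here.

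- **Scale.** A mean of grades treats every one-grade step as equal. A difference of a fraction of a grade shows a direction and an average size, but not where on the scale patients moved. Someone who starts at grade 0 cannot improve.
- **Baseline.** Subtracting the day-0 grade carries its noise into the outcome. Using it as a predictor removes noise instead. Under the protocol's rule, day-0 mRS enters the model only if it happens to be imbalanced, which is not when adjustment pays off in general.
- **Reporting.** Mean, SD, median, minimum and maximum do not show the grade distribution by arm.

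The Outcome Measurements section uses the mRS, with three other scales, to assess functional improvement. What is at stake is how sensitive and readable one exploratory result will be. The protocol states both the variable type and the test, so an analysis plan that follows it would carry the choice forward.

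**Working it through.** **Sample size used below.** No figure in the protocol is tied to the mRS, so the simulations use the evaluable number for the primary endpoint. With P1 = 0.017, P2 = 0.125, mean 0.071, difference 0.108, two-sided 5% and 80% power:

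- n0 = [1.96·√(2·0.071·0.929) + 0.8416·√(0.017·0.983 + 0.125·0.875)]² / 0.108² = (0.7119 + 0.2989)² / 0.011664 ≈ 87.6.
- With continuity correction: (87.6/4)·[1 + √(1 + 4/(87.6·0.108))]² ≈ 105.3, so 106 per group.
- Dropout: 106/0.9 = 117.8, so 118.

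Both figures match the protocol.

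**Assumed inputs.** The protocol gives no mRS distribution, correlation or effect size. Two sets were assumed, in both of which a latent disability score is cut into grades:

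- Set A: day-0 grades 0–5 at 5/30/28/20/15/2%; control day-720 grades 0–6 at 22/35/20/11/7/2/3%; latent shift 0.38 SD (common odds ratio about 1.9).
- Set B: day-0 grades 0–5 at 10/30/30/18/11/1%; control final grades 0–6 either mild (25/35/20/10/6/1/3%) or moderate (10/20/22/20/18/4/6%); common odds ratio 2.0.

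**Validity.** With no effect, a test on mean change at one visit rejected in 3–5% of trials (set A) and in 5.3% and 6.3% (set B). With 400 to 600 trials the standard error is about 1 point, so all are compatible with 5%.

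**Why baseline matters.** Suppose equal variance σ² at each visit, correlation b between day 0 and each later visit, and r between later visits. The mean of eight visits has variance σ²(1 + 7r)/8 = Vσ². Then:

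- variance of unadjusted mean change = σ²(V + 1 − 2b);
- residual variance with day 0 as covariate = σ²(V − b²).

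For b = 0.4, r = 0.6: V = 0.65, giving 0.85 against 0.49, a ratio of 1.73. For b = 0.6, r = 0.7: V = 0.7375, giving 0.5375 against 0.3775, a ratio of 1.42. Adjustment helps in both cases, and less as b rises.

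**All eight visits, simulated power** (linear analysis of the group effect averaged over visits; three sets of assumed correlations):

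| Effect over time | Unadjusted change | Day-0 mRS added | Gain (points) |
|---|---|---|---|
| Constant | 83% | 96% | 13 |
| Constant | 85% | 94% | 9 |
| Constant | 93% | 97% | 4 |
| Growing | 39% | 55% | 16 |
| Growing | 44% | 53% | 9 |
| Growing | 54% | 60% | 6 |

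**Ordinal modelling alone** (one final visit, both models with day-0 mRS):

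| Scenario | Linear | Proportional odds | Gain (points) |
|---|---|---|---|
| A, correlation 0.4 | 77% | 78% | 1 |
| A, 0.5 | 82% | 84% | 2 |
| A, 0.6 | 85% | 87% | 2 |
| A, 0.7 | 89% | 92% | 3 |
| B mild, 0.4 | 78.2% | 83.8% | 5.6 |
| B mild, 0.7 | 91.2% | 94.3% | 3.1 |
| B moderate, 0.4 | 82.8% | 85.3% | 2.5 |
| B moderate, 0.7 | 96.5% | 97.0% | 0.5 |

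Seven of the eight gains lie between 0.5 and about 3 points. A longer rerun of the mild 0.4 scenario gave the same difference, so 5.6 is not simulation noise.

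**The case against.** The strongest objection is that this is a choice of method for an exploratory scale that drives neither the sample size nor the primary conclusion. The planned test holds its level, and a mean difference still conveys direction and average size. The plan also reports the median and range. Most of this stands, and it is why the point is minor.

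Two stronger readings are tempting, and the documents do not support them.

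- *A reader might infer that calling the mRS continuous discards much of its information or leaves a result with no clinical content.* At a single visit, moving from a baseline-adjusted linear model to an ordinal one adds only a few points. In set B, mean change also kept more power than splitting the mRS at 0–1 or 0–2 (44–72%).
- *A reader might infer that an ordinal test at day 720 would clearly beat the plan.* The plan is a repeated-measures analysis, not a day-720 test. Under a constant effect, the all-visit group effect on unadjusted change had 83–93% power, against 79–84% for a day-720 proportional-odds model. Under a growing effect the order reversed, 39–54% against 76–87%; the group-by-time term, which targets that pattern, was not simulated. Dropping seven visits is a trade-off, so the fix should keep them.

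It can also be said that the protocol already allows baseline covariates and that grade tables belong in the analysis plan. The covariate rule is triggered only by a significant imbalance, so it does not plan for day-0 mRS. A grade table could indeed appear in a fuller document. The declared variable type and test, however, are stated here.

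**Conclusion.** The point holds as a cheap improvement of low severity. The mRS is misplaced in a list of continuous change scores. The planned test is valid, but it leaves out a useful predictor and yields a mean difference that is hard to interpret clinically.

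The size is about 4 to 16 points of power from adding day-0 mRS with all visits kept. Ordinal modelling adds about 0.5 to 6 points, mostly 1 to 3, at a single visit. The case for the ordinal model is therefore mainly that its result can be read.

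These figures rest on assumed grade distributions, correlations and effect sizes. The all-visit gain was tested with a linear model; the all-visit ordinal model proposed below was not itself simulated. Type I error was checked at a single visit, as a proxy for the full ANOVA.

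**What to change.** In the Analysis of Secondary Efficacy and Exploratory Endpoints section:

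1. Take the mRS out of the list of continuous change scores.
2. Analyse the mRS grade at all post-baseline visits with a repeated-measures ordinal (cumulative-logit) model, with treatment, visit, treatment-by-visit and day-0 mRS as covariates. State in advance whether the model is marginal or uses a random intercept, because the two odds ratios differ in meaning.
3. Report the common odds ratio with its confidence interval, including at day 720, and the grade distribution by arm.
4. Keep mean change as description only.

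The cost is a few lines of wording and a standard model in the SAS software already named, with no new data. The article reports 12 participants randomized and no analysis done by November 13, 2024, so on that status the change could be made without knowledge of results. One small downside is that the common odds ratio assumes a similar shift across grades, which the grade distribution by arm lets readers check.

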### Secondary Endpoints: FSS, FAS, K-PHQ-9, Pattern Identification

The FSS is a 9-item, self-reported screening tool developed by Krupp et al [26] that assesses fatigue over the past week on a scale of 1 to 7 per item, with higher total scores indicating higher levels of fatigue. The FAS is a 10-item, self-reported screening tool developed by Michielsen et al [27] that examines the psychometric qualities due to fatigue on a scale from 1=“Never” to 5=“Always” per item, with a higher total score indicating higher levels of the psychological impact of fatigue. The PHQ-9, developed by Kroenke et al [28] was validated in the Korean version [29]. It comprises 9 items in total. Respondents rate the frequency of symptoms on a scale of 0-3 per item, with a total score of 10 or higher indicating major depression. These secondary endpoints will assess the clinical effectiveness of HH333 on poststroke fatigue and depression. Pattern identification is a unique diagnostic system in Korean medicine, and the diagnosis of stroke is based on 4 patterns which are fire heat, Dampness-phlegm, Qi deficiency, and Yin deficiency [30]. Jung et al [31] developed an equation model that predicts the probability of each pattern identification diagnosis given variables for stroke pattern identification and is being used for Korean medicine's standardized diagnosis of patients with stroke. Using a stroke pattern identification prediction model, the change in each pattern identified after HH333 administration was collected to obtain data for stroke treatment in Korean medicine. Investigations were conducted during the administration period on days 0 (baseline), 90, 180, 270, 360, 450, 540, 630, and 720.

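### Read as the classical method, repeated measures ANOVA on eleven change scores over eight post-baseline visits keeps only complete attenders, not the declared full analysis set; a likelihood-based mixed model should be named instead

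*Protocol article*

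**What the plan says.** All references are to the protocol article.

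- **Endpoints.** The secondary endpoints are the total scores of FSS, FAS and K-PHQ-9; in addition, "the probability of each type of Pattern Identification (fire heat, dampness-phlegm, qi deficiency or yin deficiency) will be evaluated as secondary efficacy endpoints" (Study Design). The exploratory endpoints are K-NIHSS, mRS, K-mBI and K-MoCA.
- **Timing.** Assessments take place on "days 0 (baseline), 90, 180, 270, 360, 450, 540, 630, and 720" (Secondary Endpoints). The exploratory endpoints follow the same schedule.
- **Test.** The section Analysis of Secondary Efficacy and Exploratory Endpoints treats all of these changes as continuous and says that "the difference between the HH333 group and the control group will be tested using repeated measures ANOVA". No other between-group test is named for them.
- **Missing data.** Statistical Analysis says: "If at any point there are missing values or participants are dropped before the end of the study, the data will be treated as missing". No likelihood-based method, imputation or missing-data assumption is named.
- **Population.** The same section makes the full analysis set the main efficacy analysis: "The full analysis set includes all data from participants with at least one efficacy assessment at the primary outcome after taking the study medication". A separate comparison uses the per-protocol set, which requires completion of the study.
- **Dropout.** The Dropout criteria in the Eligibility textbox include adverse events or comorbidities, refusal of treatment, and study-medication compliance below 80%. Interventions applies the compliance limit at any point in the study. Sample Size allows for 10% dropout.

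**The concern.** Classical repeated measures ANOVA works on complete vectors. If missing values stay missing, one absent visit out of eight removes the participant from the test, including the visits that were observed. Over two years of face-to-face assessment this happens easily.

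Two things are at stake. The first is the population: the analysed group becomes close to the completers, whom the article reserves for the separate per-protocol comparison. The second is validity: a completers-only comparison is unbiased in general only if dropout is unrelated to the scores and to treatment. The listed reasons for leaving (adverse events, comorbidities, refusal, low compliance) can plausibly relate to fatigue, depression, function or assigned arm.

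**Working it through.** **Counts.** Secondary: 3 scale totals + 4 pattern probabilities = 7. Exploratory: 4. Post-baseline visits: days 90, 180, 270, 360, 450, 540, 630 and 720 = 8.

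**The plan's own figure.** The sample size concerns the primary endpoint only. A two-sided, continuity-corrected comparison of 0.017 with 0.125 at 5% and 80% power gives 106 per group. Then 106 / (1 − 0.10) = 117.8, so 118 per group and 236 in total. Both stated figures reproduce, and the 10% is an allowance for loss on top of the 212 needed.

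**Complete attenders.** Let d = 0.10 (Sample Size) and let m be the chance that a participant who stays in the study misses any one visit, independently across visits. The documents give no value for m, so a range is assumed. The share with all eight visits is (1 − d)(1 − m)^8.

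| m (assumed) | Share complete | Kept of 236 | Removed |
|---|---|---|---|
| 0% | 0.900 | 212 | 24 (10%) |
| 1% | 0.9 × 0.99^8 = 0.830 | 196 | 40 (17%) |
| 2% | 0.9 × 0.98^8 = 0.766 | 181 | 55 (23%) |
| 3% | 0.9 × 0.97^8 = 0.705 | 166 | 70 (30%) |
| 5% | 0.9 × 0.95^8 = 0.597 | 141 | 95 (40%) |

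**Precision.** Dropout costs every method information, so the fair reference is the 90% who do not drop out. The standard error then grows by 1/√((1 − m)^8):

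- 2%: 1/√0.851 = 1.08
- 3%: 1/√0.784 = 1.13
- 5%: 1/√0.663 = 1.23

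Measured against those actually seen at day 720, the 2% figure is √(0.882/0.766) = 1.07, with 0.882 = 0.9 × 0.98. The 3% and 5% figures become 1.11 and 1.20.

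**Bias, as illustration only.** A simulation used no true effect, 118 per group, eight visits with AR(1) correlation 0.7, and 300 replicates. Control dropout depended on the last score, while active dropout was random. All of this is assumed.

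- About 9% dropout in each arm: the completers-only difference was biased by about 0.05 SD, with type I error about 6%.
- About 17% control and 8.5% active: bias was about 0.10 SD, with type I error about 20%.
- A likelihood fit to all observed visits was biased by less than 0.01 SD in both cases.

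This shows the direction of risk. It is not a forecast for this trial.

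**The case against.** **The deletion is inferred.** The article never says that a participant with a missed visit is removed. Treating data as missing may simply mean no imputation, which is also how a mixed model handles them, and the full analysis set is said to include all data. The authors may be using the term loosely for a likelihood model. This stands as a limit on certainty. It does not settle the point, because the method named is not a likelihood model in its usual meaning and nothing in the text makes it one.

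**Detail belongs in the SAP.** Covariance structure and target contrast are commonly left there, so their absence is not criticised. The point rests on what the article does fix: the test, the missing-data rule and the main population.

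**Stronger readings that the documents do not support.**

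- A reader might quote standard errors 14%, 19% or 29% larger (1/√0.766, 1/√0.705, 1/√0.597). Those compare with 100% complete data, which no method achieves at 10% dropout.
- A reader might infer that participants who deteriorate after a recurrence are the ones lost. Recurrence is not a listed dropout criterion, and nothing documents such a pattern.
- A reader might fault the sphericity assumption. The between-group main effect does not need it; only the visit and group-by-visit tests do.
- A reader might say that baseline is ignored. Change scores use it by subtraction, and Demographic Information Analysis admits baseline variables that differ significantly as covariates. Routine adjustment would add precision rather than remove a bias.

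**The assumed rates may be pessimistic.** Clustered misses would leave more complete cases, and some missed visits may already sit within the 10%, since medication is supplied at visits and low compliance leads to dropout. That is fair, and it is why a range is shown.

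**Conclusion.** The point holds as a cheap and worthwhile improvement to the secondary and exploratory analyses. Read as the classical method, the stated test conflicts with the stated main population and needs completely random dropout, which the protocol's own dropout criteria make doubtful.

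The loss is about 24 of 236 participants at the planned dropout alone, if it falls before day 720, and about 55 of 236 with 2% of visits also missed. The precision cost of missed visits is about 8% to 23% on the standard error for assumed rates of 2% to 5%, independent across visits. Any bias depends on dropout patterns that the documents do not give; the simulated 20% type I error needs differential dropout that nothing in them establishes.

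The primary logistic regression and the sample size are not touched.

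**What to change.** In Analysis of Secondary Efficacy and Exploratory Endpoints, replace repeated measures ANOVA with a likelihood-based mixed model for repeated measures on all observed post-baseline scores. Terms: treatment, visit, treatment-by-visit, baseline score and baseline-by-visit, with unstructured covariance across the eight visits. Report the day-720 treatment difference with its 95% CI for each scale. If the authors already intend such a model, one sentence saying so is enough.

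This keeps every participant with at least one post-baseline score. Someone in the full analysis set through the day-30 recurrence check who leaves before day 90 would still contribute nothing, so the number analysed should be reported for each scale.

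The cost is a few lines of text and routine code in SAS, the software already named. The downsides are slightly more complex modelling and a missing-at-random assumption, which is weaker than completely random dropout but still an assumption. With 12 participants randomized and no analysis done at the time of the report, the change could be made without knowledge of results. An ordinal model for mRS, a 0 to 6 scale, is optional.

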### Demographic Information Analysis

For each group, continuous data yielded the mean, SD, median, minimum, maximum, and 95% CIs, whereas categorical data yielded frequencies and percentages. To compare groups, we used a two-sample *t* test or Wilcoxon rank-sum test for continuous data, and a chi-square test or Fisher’s exact test for categorical data. Baseline information that was recognized as significantly different between the 2 groups was considered a covariate in the efficacy analysis to correct for heterogeneity between the treatment groups.

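### The secondary and exploratory change scores are adjusted for the day-0 score at most when it differs significantly between arms, which costs precision and leaves estimates exposed to smaller chance imbalances

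*Protocol article*

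**What the plan says.** Analysis of Secondary Efficacy and Exploratory Endpoints defines the secondary outcomes as "FSS, FAS, K-PHQ-9 total score change, each pattern identification probability change". With four patterns, that is seven endpoints. It adds that "exploratory endpoints K-NIHSS, mRS, K-mBI, K-MoCA total score change are continuous variables", which makes four more and 11 in all. For every one of them, "the difference between the HH333 group and the control group will be tested using repeated measures ANOVA". The section names no covariate.

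The one covariate rule for efficacy stands under Demographic Information Analysis: "Baseline information that was recognized as significantly different between the 2 groups was considered a covariate in the efficacy analysis". The section does not say whether baseline information means demographic and clinical characteristics only, or also the day-0 outcome scores.

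The scores are taken at baseline and at eight later visits: "Investigations were conducted during the administration period on days 0 (baseline), 90, 180, 270, 360, 450, 540, 630, and 720". On the error rate: "All statistical analyses were two-sided with a 5% significance level".

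**The concern.** A change score subtracts the whole baseline value. When the correlation rho between baseline and follow-up is below 1, that is too much. An arm that starts worse by chance will appear to improve more through regression to the mean. Including the day-0 score as a covariate subtracts the right fraction and removes the variance that baseline explains.

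The stated rule does this only after a significant baseline test. In a randomised trial that test detects chance differences only, and its p-value says nothing about how strongly the score predicts follow-up. The model for each endpoint then depends on the data.

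These endpoints carry the fatigue, depression and pattern-identification questions and, at exploratory level, the neurological and functional ones. At stake are the precision of those comparisons and how far each estimate reflects who happened to be allocated where.

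**Working it through.** **The plan's own figure.** The only computed figure in the article is the primary-endpoint sample size. Two proportions, 0.017 against 0.125, two-sided 5%, 80% power, with continuity correction, give 106 per arm. Then 106/0.90 = 117.8, so 118. Both stated figures reproduce. Only the 106 per arm is used below.

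**Inputs.** 106 per arm (Sample Size); eight post-baseline visits (Secondary Endpoints section); two-sided 5% (Statistical Analysis). Assumed, because the documents give no value: rho from 0.3 to 0.9, and equal variance s² at baseline and follow-up.

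**1. One visit, no adjustment.** Per-patient variance of change is 2(1−rho)s². With the day-0 score as covariate (ANCOVA) it is (1−rho²)s². The ratio of ANCOVA to change is (1+rho)/2, so the information lost is (1−rho)/2.

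**2. One visit, adjustment only if baseline differs at p<0.05.** The unadjusted estimate carries an extra variance term (1−rho)² from baseline imbalance. Adjusting only when the standardised imbalance exceeds 1.96 leaves the share E[Z²; |Z|<1.96] = 0.95 − 2×1.96×0.0584 = 0.72 of that term. The loss is 1 − (1−rho²)/[(1−rho²) + 0.72(1−rho)²].
- rho 0.5: 1 − 0.75/(0.75+0.18) = 19%
- rho 0.7: 1 − 0.51/(0.51+0.065) = 11%

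A simulation of 20,000 trials with 106 per arm gave 18.9% and 11.2%.

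**3. Mean of the eight visits, no adjustment, compound symmetry.** Let V = (1+7rho)/8. Change has variance V+1−2rho and ANCOVA has V−rho².
- rho 0.5: V = 0.5625; 1 − 0.3125/0.5625 = 44%
- rho 0.7: V = 0.7375; 1 − 0.2475/0.3375 = 27%

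| rho (assumed) | One visit, unadjusted | One visit, triggered rule | Mean of 8 visits, unadjusted |
|---|---|---|---|
| 0.3 | 35% | not computed | 62% |
| 0.5 | 25% | 19% | 44% |
| 0.7 | 15% | 11% | 27% |
| 0.9 | 5% | not computed | 9% |

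**4. In terms of power.** If ANCOVA at one visit had 80% power, the unadjusted change score would have Φ(2.80×√((1+rho)/2) − 1.96): 67.9% at rho 0.5, 73.3% at 0.7 and 78.0% at 0.9.

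**5. Imbalance that escapes the trigger.** The standard error of the baseline difference is √(2/106) = 0.137 SD, so a difference up to 1.96×0.137 = 0.27 SD is not significant. The change score over-corrects by (1−rho) times the imbalance: at 0.27 SD, 0.13 SD for rho 0.5 and 0.08 SD for rho 0.7, against the direction of the imbalance. In the simulation, the correlation between the estimated effect and the baseline imbalance was −0.37 (rho 0.5) and −0.30 (rho 0.7) under the triggered rule, and about 0 with ANCOVA.

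**6. Mixed models across endpoints.** If the rule covers the 11 baseline scores and they were independent, the chance that at least one triggers is 1 − 0.95^11 = 43%. Some endpoints could then be adjusted and others not. The scores are likely correlated, so this figure is only indicative.

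**The case against.** The strongest reply is that this is a condensed article. It names a family of methods without listing model terms, and a covariate list for secondary models commonly belongs in an analysis plan that is not shown. That stands as far as silence goes: the absence of a baseline term from the repeated measures section would not be a finding by itself. The covariate rule, however, is stated, and an analysis plan that followed it would carry the weakness forward.

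Several stronger readings are tempting, and the documents do not support them.
- A reader might infer that baseline adjustment is ruled out. It is not; the covariate rule may allow it, conditionally.
- A reader might take a 15–25% loss as a property of this trial. That range needs rho between 0.7 and 0.5, one visit and no adjustment. The article states no correlation, plans eight post-baseline visits and has the conditional rule.
- A reader might infer bias or an inflated error rate from using change scores. Over randomisations the unadjusted change comparison is unbiased and its test is valid. Imbalance does not pass through in full either; only the (1−rho) over-correction remains.
- Power gains simulated for a single scale at a single visit, such as mRS under an assumed shift, would not carry over to all 11 endpoints.

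It is also fair that the trial is called a pilot, that four of the scores are exploratory, and that no power is claimed for any of the 11.

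**Conclusion.** The point holds as one of efficiency and pre-specification. Under the text as written, the day-0 score enters each comparison about 5% of the time per score, or never, depending on what the covariate rule covers. On neither reading is it routinely in the model. The loss is positive at every rho below 1. Its size rests wholly on an assumed correlation, on equal variances and, for the eight-visit mean, on compound symmetry, so it should be quoted as a range. The triggered rule reduces the loss but does not remove it, and imbalances up to about 0.27 SD remain unadjusted.

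The primary logistic regression and the sample size are not part of this point. The change should be made, but the trial's main conclusion does not depend on it.

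**What to change.** In Analysis of Secondary Efficacy and Exploratory Endpoints, state that every repeated-measures model includes the day-0 value of the same score and its interaction with visit, whatever the baseline comparison shows. Change can remain the reported outcome: with baseline in the model, the group difference is the same whether change or the follow-up score is analysed. In Demographic Information Analysis, remove selection of covariates by significance for these analyses and keep the baseline table descriptive in that respect.

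The cost is one covariate and its visit interaction per model. Day-0 scores are already scheduled at visit 1 in Table 1, so no extra patients, visits or measurements are needed. The Results section reports that no data had been analysed, so on that account the change could be made without knowledge of outcomes. An ordinal model for mRS is an optional, separate choice and is not needed to resolve this point.
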